### Outcomes

#### Primary outcome

The primary endpoint is the early postoperative QoR, assessed via the French version of the QoR-15 questionnaire score (FQoR-15) [19] and measured at 24 h after the surgery (H24). The Quality of Recovery-15 (QoR-15) is one of the most reliable and reproducible tools for assessing the QoR after surgery [20–22]. The use of this tool as an endpoint has been recommended by a recent international consensus [23] and has already been measured in previous randomized trials [24].

The FQoR-15 is obtained via a self-administered questionnaire, consisting of 15 items scored on an 11-point scale with an overall score (sum of each item) ranging from 0 to 150 (0 for very bad recovery, 150 for excellent QoR). The questionnaire will be given by the nurses to the patient in ICU on a paper sheet that will be filled out by the patient.

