#### Secondary outcomes

In order to evaluate the impact of a SPIP or DPIP on the QoR, we will also reassess the QoR-15 score at 48 h (H48) and 72 h (H72) after the surgery. We will compare analgesic efficacy at rest and during exercise (cough, physiotherapy, mobilization) between the different groups via a pain intensity evaluation using a numeric rating scale (NRS, 11 items, 0 for no pain and 10 for the maximum pain) up to H72 after the surgery and during the removal of the drains at 24 h after surgery (H24). We will specify the proportion of painful patients (defined by an NRS value > 3) at H24 and H48. We will also collect the main area of pain during the first 24 h after surgery between the back, the head, the thorax, the abdomen, and the saphenous scar. We will also compare the postoperative consumption of analgesics (both morphine equivalents and non-opioid drugs) up to 5 days after the surgery.

The tolerance of the technique will be compared by assessing the proportion of patients with at least one local complication of regional anesthesia: systemic intoxication to local anesthetics within 3 h after injection, hematoma or infection at the puncture site during the 30 days after the surgery (D30). We will also compare in each group the proportion of patients with at least one major hospital postoperative complication [25] (the complete list is presented in Table S.2 in the supplementary materials).

We will assess in each group the proportion of patients with a return to preoperative weight, as the proportion of patients with bowel movements assessed on days 3 and 5 after surgery. We will compare the delay of extubation (measured between the admission in ICU and the first attempt of extubation), the length of stay in ICU, and the length of hospital stay censored at D30 if the patient is still hospitalized. The readmission rate in ICU will be specified at D30.

The anesthetist’s satisfaction with the ease of performing the technique (i.e., DPIP or SPIP) will be evaluated on a 5-item Likert scale (not at all satisfied, not very satisfied, neutral, fairly satisfied, very satisfied) and compared between the two intervention groups with blocks.

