### Statistical analysis

All analyses will be performed using the R software (version 4.1.3). The main analysis will be in intention-to-treat, including all randomized patients. Patients will be analyzed according to their randomization group. A per-protocol analysis will be performed as a sensitivity analysis to assess the main robustness analysis. A flow chart of all patients (Fig. 2) and descriptive statistics will be used to describe baseline characteristics. Data will be presented by their mean with standard deviation, median with interquartile range, according to their normal or non-normal distribution respectively, and number with the percentage of sample (%). For the endpoint comparisons, we will report both absolute measures (differences in means or percentages) and relative measures (odds ratios or hazard ratios), with their 95% confidence interval.

We will detail the missing data on the endpoints involved in the type I error hierarchical management only. We will identify the status of these missing data for these criteria between completely randomly missing, randomly missing, or non-randomly missing. For criteria with less than 10% missing data, we will not perform a missing data management method. For criteria with more than 10% missing data on these criteria, we will perform sequential multiple imputations by chained equations (mice package in R, with 5 imputations, from predictors/variables at inclusion, set.seed 1111). If the multiple imputation method is used (i.e., more than 10% missing data), we will study the impact of the data imputation. We will then carry out an analysis of the concrete cases, as well as the following sensitivity analyses: “best–worst” and “worst-best.” For the “best–worst” scenario, it is assumed that all patients lost to follow-up will have a beneficial outcome, whereas in the “worst-best” scenario, they will have a negative outcome. For the continuous outcomes, the beneficial outcome will be the mean value of the group plus one standard deviation, while the adverse outcome will be the mean minus one standard deviation.

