For all analyses using regression models, the included covariates will be the allocation group, as well as the stratification group (surgery with or without thoracic internal arterial graft). For analyses requiring a mixed model, the covariates introduced will be a fixed effect for the treatment arm, a fixed effect for the stratification factor, a fixed effect for the time frame of the visit, and a random effect for the patients, and under an unstructured variance/covariance matrix. If the mixed models do not converge, we will use a compound symmetry correlation structure. To address the main objective, we will use a linear regression model. Similarly, the QoR-15 score at H48 will be analyzed using a linear regression model. The evolution of effort pain up to H48 will be analyzed using a linear mixed model. The evolution of morphine equivalent consumption will be analyzed using a mixed model, following a Poisson distribution. The rate of occurrence of at least one postoperative complication will be compared by logistic regression. Censored 30-day hospital stay will be assessed by survival analysis using a semi-parametric Cox model.

The other endpoints will not have a method of imputation for missing data. Thus, only those individuals for whom endpoints are available will be included in the analyses. These data will be analyzed for exploratory purposes. The evolution of pain at rest will be analyzed with a linear mixed model, and we will compare the evolution of the consumption of non-opioid analgesic drugs with a mixed model, following a Poisson distribution. The proportions of patients with pain at H24 and H48, as the rate of local and systemic complications during the follow-up will be compared using logistic regression. The total hospital consumption of morphine equivalent in the first 72 h will be assessed by Poisson regression. Pain intensity at the pericardiac drain removal at H24 will be assessed by linear regression. Time to resuscitation censored at 30 days, time to extubation, time to recover bowel movements, and time to return to preoperative weight will be assessed by survival analysis using a semi-parametric Cox model. The distribution of postoperative complications will be compared by multinomial regression. Satisfaction with the block procedure and the main painful area at H24 will be presented descriptively in the groups.

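### The scenario fill-in rule is signed correctly for QoR-15 but backwards for effort pain (and for morphine consumption, if it counts as continuous), so the best–worst and worst–best labels would be exchanged for those endpoints

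*Protocol article*

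**What the plan says.** All of this is in the Protocol article.

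- **Scenarios (Statistical analysis).** When an endpoint in the type I error hierarchy has more than 10% missing data, multiple imputation is used and two scenario analyses follow. The article describes best–worst first and then its counterpart: "it is assumed that all patients lost to follow-up will have a beneficial outcome, whereas in the “worst-best” scenario, they will have a negative outcome".
- **Fill-in values (Statistical analysis).** On continuous endpoints the rule reads "the beneficial outcome will be the mean value of the group plus one standard deviation". The unfavourable counterpart stands in the same sentence: "the adverse outcome will be the mean minus one standard deviation". Nothing makes the sign depend on the direction of the endpoint.
- **Directions of the scales.** QoR-15 runs upward: "0 for very bad recovery, 150 for excellent QoR" (Primary outcome). Pain runs downward: "0 for no pain and 10 for the maximum pain" (Secondary outcomes). The Background presents opioid sparing as an aim, so lower morphine consumption is the better result.
- **Planned models (Statistical analysis).** Pain on effort gets a linear model: "The evolution of effort pain up to H48 will be analyzed using a linear mixed model". Opioid use gets a model of another type: "The evolution of morphine equivalent consumption will be analyzed using a mixed model, following a Poisson distribution".

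**The concern.** The scenarios are defined by whether an outcome is good or bad, but the sentence that turns this into numbers fixes one arithmetic direction for all continuous outcomes. On a scale where lower is better, one SD above the mean is the worse value. For effort pain, the scenario described as beneficial would therefore insert above-average pain, and the one described as negative would insert below-average pain.

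Two things are at stake. First, each scenario result for a lower-is-better endpoint would be reported under the opposite name. Second, one named scenario would not mean the same thing across the hierarchy: it would fill QoR-15 and the binary complication endpoint favourably, and pain and morphine unfavourably.

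**Working it through.** **Does the rule reach these endpoints?** The section on type I error management says that the hierarchy continues from the primary endpoint to several secondary endpoints. The Statistical analysis section confines missing-data handling to hierarchy endpoints. It then gives models for QoR-15 at H48, effort pain up to H48, morphine-equivalent consumption, complications and hospital stay, and goes on to say that the other endpoints get no imputation. The first list therefore reads as the hierarchy set. This is a strong inference, but Fig. 3 is not shown. Complications are binary and hospital stay is analysed as a censored time, so I do not count them as continuous here. Morphine is modelled as Poisson, so whether it counts as continuous is open; if it does not, the article gives it no fill-in value.

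**Inputs.** From the article: the rule, the 10% trigger, the scale directions, and a QoR-15 mean of 90 with SD 18 (Sample size). The article gives no mean, SD or missing rate for pain or morphine. My assumptions are effort-pain mean 3 to 5 and SD 2 to 2.5; morphine mean 20 mg and SD 15 to 25; missing effort-pain scores 18% in SPIP and 8% in DPIP.

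**Step 1: the rule on QoR-15.** Beneficial = 90 + 18 = 108; adverse = 90 - 18 = 72. Higher is better, so the direction is right.

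**Step 2: the rule on effort pain.**

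| Assumed mean, SD | Filled as beneficial | Filled as adverse |
|---|---|---|
| 3, 2 | 5 | 1 |
| 4, 2 | 6 | 2 |
| 5, 2.5 | 7.5 | 2.5 |

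Mean + SD exceeds mean - SD for any SD above zero, so the reversal depends on none of the assumed figures. With mean 4, SD 2 and 20% missing, the arm mean becomes 4 + 0.20 × 2 = 4.4 under the beneficial fill and 4 - 0.20 × 2 = 3.6 under the adverse one.

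**Step 3: effect on the group difference.** The rule gives all lost patients the same kind of fill, whichever arm they are in. With missing fractions mD and mS and a common SD, the beneficial scenario shifts DPIP minus SPIP by:

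- as written: (mD - mS) × SD
- as meant for a lower-is-better endpoint: -(mD - mS) × SD

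With mD = 0.08 and mS = 0.18 (an average of 13% over these two arms, above the trigger):

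| SD | As written | As meant |
|---|---|---|
| 2 | -0.10 × 2 = -0.20 | +0.20 |
| 2.5 | -0.10 × 2.5 = -0.25 | +0.25 |

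With equal missingness, for example 15% in each arm, the shift is (0.15 - 0.15) × SD = 0 whichever sign is used.

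**Step 4: morphine, if the rule applies to it.** With mean 20 mg, the adverse value is 20 - 15 = 5 mg at SD 15 and 20 - 25 = -5 mg at SD 25. Whenever the SD exceeds the mean, the value is negative, which is impossible as a consumption and cannot be an outcome in a Poisson model.

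**The case against.** The intent is clear. The scenarios are described by outcome quality, the SD sentence was evidently written with QoR-15 in mind, and an analyst who follows the description would choose the right sign. That limits the harm but does not remove the error, because an analyst who follows the stated formula gets the wrong sign.

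The reach is also narrow. The rule applies only above 10% missing data, and the only missing rate that the article plans for is at most 5%, for the primary endpoint. QoR-15 is signed correctly, so both hierarchy comparisons on the primary endpoint, and QoR-15 at H48, are untouched. All of this stands.

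A reader might infer more than the document supports, in three ways:

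- **That a favourable result is shown in place of an unfavourable one.** Both scenarios are run. For pain, the two results are the same pair and span the same range; only the names are exchanged.
- **That the error can move the pain difference by more than a point.** That would need opposite fills in the two arms. The article assigns the same kind of outcome to all lost patients, so such figures belong to a rule that it does not state.
- **That negative pain scores would be created.** Within the assumed ranges, the lowest adverse value is 3 - 2.5 = 0.5, which is still on the scale.

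The negative-morphine point is likewise conditional. It needs morphine to be treated as continuous and an SD above the mean, and the article gives no figures on the second condition.

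**Conclusion.** The rule is wrong as written for lower-is-better continuous endpoints. For effort pain up to H48, and for morphine consumption if it is treated as continuous, the best–worst and worst–best results would each carry the opposite label, and one scenario name would mean opposite things across the hierarchy. That these endpoints belong to the hierarchy is inferred from the text.

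The consequence is modest: mislabelling in a sensitivity analysis of secondary endpoints that is run only above 10% missing data. The main analysis is not affected. The size under the rule as written is the sign reversal in step 3, a few tenths of an NRS point under an assumed imbalance in missingness and an assumed SD, and nothing when missingness and SDs are equal. A scenario that cannot be computed for morphine is a possibility, not a demonstrated result.

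**What to change.** Replace the sentence on continuous outcomes with one that follows the direction of each endpoint, for example:

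> *For QoR-15 the beneficial value is the group mean + 1 SD and the adverse value the mean - 1 SD. For pain and morphine-equivalent consumption the beneficial value is the group mean - 1 SD and the adverse value the mean + 1 SD. Filled values are truncated to the possible range of the endpoint (QoR-15 0 to 150, NRS 0 to 10, consumption at or above 0).*

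Naming morphine here also settles whether the rule covers it, and the truncation deals with the conditional negative value. The cost is one sentence, plus a sign and a truncation in the sensitivity-analysis code. No data, sample size or main analysis changes. If a separate analysis plan already has the correct sign, the two texts should be reconciled before the unblinded analysis.

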### Sample size

In the database used to validate the FQoR-15 questionnaire, 21 patients were operated on for cardiac surgery with sternotomy, and the average FQoR-15 score was 90 ± 18. The minimal important difference of the QoR-15 score is usually set at 8.0 [26].

We assume that the DPIP has a greater impact than the SPIP on QoR, and we set mean QoR-15 values of 98 in the SPIP group and 106 in the DPIP group.

The management of comparisons and the type I error risk will be performed in a sequential hierarchical strategy (Fig. 3). First, we will compare the primary endpoint (QoR-15 value at H24) between the interventional groups (patients in the SPIP and DPIP groups combined) with the standard group. If efficacy is revealed by this first comparison, further comparisons will be performed between the SPIP and DPIP groups only. Considering a type I error risk of 0.05 in a two-sided test and a statistical power of 0.8, 80 patients will be needed in each intervention group (i.e., SPIP and DPIP) to obtain the minimum power to conclude on the comparison between both groups. With 80 patients in the standard group, we expect to achieve greater than 95% power in the first analysis of the primary outcome (interventional groups versus standard group). Considering our three groups (SPIP, DPIP, and standard groups) and assuming a maximum rate of 5% of patients for whom the primary endpoint will not be available, we plan to include 254 randomized patients.

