### Follow-up

Day 0 (D0) is the day of surgery with hour 0 (H0) corresponding to the time of randomization. The delay between randomization, achievement of the intervention for the arms with PNB, and admission to the ICU will be negligible (a few minutes). Ten visits are scheduled after the inclusion, and the summarized plan is presented in Fig. 1. The follow-up will begin at the pre-inclusion visit during the anesthesia consultation aiming to collect demographic data, type of surgery, medical history, vitals parameters (cardiac rate and blood pressure), and the pre-operative QoR-15 score.

The inclusion visit will be realized at the end of the surgery during the skin closure. Once the patient is included and allocated to one arm, the block will be carried out according to the allocation group before the transfer to the ICU. The operator’s satisfaction will be assessed on a Likert scale at this time. Perioperative surgical and anesthesia data will be recorded.

On ICU admission, the collected data will be the hemodynamic parameters, the biological values, and a local or systemic complication possibly linked to block. The intensity of pain at rest and during effort, the consumption of analgesics, and the notification of local or systemic complications will be collected during the following visits at 3, 6, 12, 24, 48, and 72 h after the surgery. The QoR-15 questionnaire will be completed at H48 and H72. At H24, patients will detail the body localization of the most intense pain, the use of a rescue peripheral nerve block, and the intensity of pain at the removal of the pericardial drains. Morphine equivalents and non-opioid analgesic drugs consumptions will be collected at 4 and 5 days after the surgery. The patient’s weight and the occurrence of bowel movement will be noted at H72 and 5 days after the surgery.

Thirty days after the surgery, the following data will be collected: a puncture site or a postoperative complication, the length of hospital censored at D30 if the patient is still hospitalized, and length of stay in ICU. Potential readmission to ICU will also be notified. If the patient’s condition does not allow him to be contacted directly or by phone, the person in charge of the follow-up will be contacted (e.g., family member or physician).

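### The QoR-15 models leave out the pre-operative QoR-15 score, giving up precision in the SPIP versus DPIP comparison, which is sized at only 80% power

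*Protocol article*

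**What the plan says.** The Follow-up section of the protocol article lists what is gathered at the pre-inclusion visit, held at the anesthesia consultation. The list includes "vitals parameters (cardiac rate and blood pressure), and the pre-operative QoR-15 score". The outcome instrument is therefore to be measured before randomization.

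The Statistical analysis section uses linear regression for the primary endpoint (QoR-15 at H24) and likewise for QoR-15 at H48. It sets the covariates once for every regression model: "For all analyses using regression models, the included covariates will be the allocation group, as well as the stratification group", the stratum being surgery with or without an internal thoracic artery graft. The only covariate sensitivity analysis it names for the primary endpoint takes the stratification factor out. Nothing in the article puts the pre-operative score into an efficacy model.

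The Sample size section sets 80 patients per block arm "to obtain the minimum power to conclude on the comparison between both groups", meaning SPIP versus DPIP. For combined blocks versus standard care it says "we expect to achieve greater than 95% power in the first analysis of the primary outcome". Under Type I error management, SPIP versus DPIP on the primary endpoint is the second step. Several secondary endpoints follow it, and they become exploratory if it fails.

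**The concern.** The baseline value of an outcome is often related to its later value. When it is, including it in a linear model removes part of the between-patient variance (the share r²) and adjusts for chance baseline imbalance between arms. The trial already plans to collect the score, so including it needs no new data.

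An unseen analysis plan would not naturally fill this gap, because the article states a closed list for all regression models and the score is not on it. Adding the score after unblinding would look data-driven.

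SPIP versus DPIP is the weak link. It has no reserve above 80%, and its planning SD comes from 21 patients. If it misses significance, the confirmatory sequence stops there.

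**Working it through.** **Inputs, all from the Sample size section**

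- Error rates: "Considering a type I error risk of 0.05 in a two-sided test and a statistical power of 0.8".
- SD 18 and standard-group mean 90: "21 patients were operated on for cardiac surgery with sternotomy, and the average FQoR-15 score was 90 ± 18".
- Block-arm means: "we set mean QoR-15 values of 98 in the SPIP group and 106 in the DPIP group", so the SPIP versus DPIP difference is 106 − 98 = 8.
- 80 patients per arm.

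**Step 1. Reproduce the plan's figure.** n per arm = 2(1.960 + 0.842)² × 18² / 8² = 79.5, which rounds up to 80. This agrees with the plan. With 80 per arm the standard error is 18√(2/80) = 2.846 and the non-centrality is 8/2.846 = 2.811. Two-sided power from the non-central t distribution is 79.8% (80.3% by the normal approximation).

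**Step 2. The first comparison.** The combined block mean is (98 + 106)/2 = 102, so the difference from standard care is 102 − 90 = 12. The standard error is 18√(1/80 + 1/160) = 2.465 and the non-centrality is 12/2.465 = 4.87. Power is about 99.8%, in line with the stated figure of more than 95%. Baseline adjustment cannot materially raise it.

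**Step 3. SPIP versus DPIP with the baseline score in the model.** The article does not give r, so 0 to 0.6 is assumed. Residual SD = 18√(1 − r²). Power is from the non-central t with 156 degrees of freedom (160 patients less intercept, arm, stratum and baseline). The r = 0 row is the unadjusted comparison of Step 1. The equivalent n per arm is 80/(1 − r²), and the 95% CI half-width is 1.96 × residual SD × √(2/80).

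| r | Variance removed | Residual SD | Power | Equivalent n per arm | CI half-width (points) |
|---|---|---|---|---|---|
| 0 | 0% | 18.00 | 79.8% | 80 | 5.58 |
| 0.1 | 1% | 17.91 | 80.2% | 81 | 5.55 |
| 0.2 | 4% | 17.64 | 81.4% | 83 | 5.47 |
| 0.3 | 9% | 17.17 | 83.4% | 88 | 5.32 |
| 0.4 | 16% | 16.50 | 86.2% | 95 | 5.11 |
| 0.5 | 25% | 15.59 | 89.7% | 107 | 4.83 |
| 0.6 | 36% | 14.40 | 93.7% | 125 | 4.46 |

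The gain is 0.4 points of power at r = 0.1, 1.6 at r = 0.2, 3.6 at r = 0.3 and 9.9 at r = 0.5.

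**Step 4. Sensitivity to the SD.** An SD of 18 from 21 patients has a normal-theory 95% confidence interval of 18√(20/χ²), about 13.8 to 26.0. If the SD were 20 (an assumption), unadjusted power would be 71.0%, rising to 82.7% with baseline adjustment at r = 0.5.

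**The case against.** The strongest reply is that nothing here is wrong. Under randomization, a linear model with allocation and the stratification factor gives a valid test. It matches the stratified design, and the sample size reproduces. Eighty percent is the trial's chosen target, and it is met. All of this stands. A reader might infer that the primary analysis is biased or the trial mis-sized, but the document supports neither reading.

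The second reply is that the gain rests on an unknown correlation. The pre-operative score is taken at a consultation about two weeks before surgery, and the outcome is taken in intensive care a day after sternotomy. A moderate r cannot be presumed across that gap, and at r = 0.2 or less the benefit is small. This also stands and limits the size of the claim. It is no reason to leave the covariate out, since power does not fall even at r = 0.1.

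The third reply concerns reach, and three broader readings fail:

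- Not every primary comparison is at 80% power. The first is far above it.
- SPIP versus DPIP does not gate every secondary test. It gates those in the hierarchy diagram, and outcomes outside it are exploratory in any case.
- The plan does not name a linear model for H72, so that time point is affected only if such a model is used.

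Finally, the baseline score is planned for collection, but its completeness is unknown. The fix therefore needs a rule for missing values.

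**Conclusion.** The point holds as an avoidable loss of precision fixed into the analysis, not as an error of validity. For SPIP versus DPIP at H24, adding the baseline score would raise power from 79.8% to between 80.2% (r = 0.1) and 93.7% (r = 0.6), and by under 2 points if r is 0.2 or less. These figures assume a difference of 8, an SD of 18, 80 analysed patients per arm, and r read as the correlation remaining after the stratum is accounted for. That the score is left out is certain from the text; how much is lost is not. The change is worth making because it costs almost nothing and helps the weaker of the two comparisons on the primary endpoint.

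**What to change.** - In the Statistical analysis section, add that the linear models for QoR-15 at H24 and H48 include the pre-operative QoR-15 as a continuous covariate, alongside allocation and stratum. Apply the same at H72 if a linear model is used there.
- State that missing pre-operative scores are replaced by the overall mean across all randomized patients, so that no patient is dropped for lack of a baseline value.
- Report the model without the baseline score as an additional sensitivity analysis. Keep the planned one that omits the stratification factor.

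The cost is a short text change and one degree of freedom, with no new visits, data or patients. The Trial status section gives a recruitment start of July 2022, so the change needs a documented amendment made before any unblinded data are seen.

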All tests will be two-sided. Statistical significance is set in the usual way with a *p*-value < 0.05, and 95% confidence intervals will be estimated for each calculated value. For the primary endpoint (QoR-15 score at H24), a sensitivity analysis will be performed without including the stratification factor in the model.

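### Total 72 h morphine-equivalent consumption is a drug amount, but plain Poisson regression is planned for it, so its standard error depends on the unit and is probably too small

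*Protocol article*

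**What the plan says.** Under Secondary outcomes the article defines the outcome as a quantity of drug: "We will also compare the postoperative consumption of analgesics (both morphine equivalents and non-opioid drugs) up to 5 days after the surgery". It states neither a unit nor a reference route for the morphine equivalents.

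The Statistical analysis section then names three Poisson analyses:

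- 72 h opioid total: "The total hospital consumption of morphine equivalent in the first 72 h will be assessed by Poisson regression". The rule for regression models is that "the included covariates will be the allocation group, as well as the stratification group". No dispersion parameter, robust variance or alternative distribution is named.
- Repeated opioid consumption: "The evolution of morphine equivalent consumption will be analyzed using a mixed model, following a Poisson distribution".
- Repeated non-opioid consumption: "we will compare the evolution of the consumption of non-opioid analgesic drugs with a mixed model, following a Poisson distribution".

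The mixed models have fixed effects for arm, stratification factor and visit time, and "a random effect for the patients, and under an unstructured variance/covariance matrix". The 72 h total has no such term.

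The 72 h total and non-opioid consumption belong to the group of endpoints of which the section says "These data will be analyzed for exploratory purposes". The section closes with a two-sided 0.05 threshold and the statement that "95% confidence intervals will be estimated for each calculated value".

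**The concern.** Poisson regression gives a sensible estimate of a ratio of means even when the outcome is not a count. The trouble is its default standard error, which is derived from variance = mean. For a count of events that is at least a coherent starting point. For an amount of drug it has no meaning, because mean and variance do not scale alike when the unit changes. The same patients and the same ratio of means would give different p-values in mg, in 10-mg units or after conversion to another reference route.

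If consumption varies between patients by more than the square root of its mean, the interval is also too short. The trial could then report a difference in opioid use between arms, with an apparently tight 95% interval, that is only patient-to-patient variation. The introduction presents opioid sparing as one aim of the analgesic strategy, so readers will look at this result.

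**Working it through.** **Inputs.** From the article: about 80 analysable patients per arm (Sample size), two-sided 0.05, 95% intervals. The documents give no mean, SD or unit for consumption, so these are assumed and varied.

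**The plan's own figure.** The 80 per arm reproduces: 2 × (1.96 + 0.842)² × 18² / 8² = 79.5, so 80. It is used here only as the group size.

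**Step 1: unit dependence (no assumption needed).** For two arms with totals S₁ and S₂, the Poisson standard error of the log ratio is √(1/S₁ + 1/S₂). Multiplying every value by c leaves the ratio unchanged and divides the standard error by √c. On one simulated data set (80 per arm):

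| Unit | Log ratio | Poisson SE | Sandwich SE |
|---|---|---|---|
| mg | 0.0155 | 0.0279 | 0.101 |
| 10-mg units | 0.0155 | 0.0882 | 0.101 |
| mg × 3 | 0.0155 | 0.0161 | 0.101 |

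**Step 2: size of the error (assumed mean and SD).** With equal arms of n and no true effect:

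- Poisson SE = √(2 / (n × mean))
- true SE = √(2 × (SD/mean)² / n)
- ratio r = true SE / Poisson SE = SD / √mean, which does not depend on n
- type I error = 2 × (1 − Φ(1.96 / r))

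| Mean / SD (mg) | Poisson SE | True SE | r | Type I error | Coverage of nominal 95% CI |
|---|---|---|---|---|---|
| 20 / 10 | 0.035 | 0.079 | 2.24 | 38% | 62% |
| 30 / 20 | 0.029 | 0.105 | 3.65 | 59% | 41% |
| 60 / 40 | 0.020 | 0.105 | 5.16 | 70% | 30% |

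The problem disappears when SD ≤ √mean. At mean 10 and SD 3, r = 3/√10 = 0.95 and coverage is 96%. The stratification covariate is left out of these calculations.

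**Step 3: simulation.** Gamma-distributed consumption, mean 30, SD 20, 80 per arm, no effect, 4,000 trials:

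| Unit | Plain Poisson | Sandwich | Quasi-Poisson |
|---|---|---|---|
| mg | 59% | 5.0% | 4.7% |
| 10-mg units | 8% | 5.0% | 4.7% |
| mg × 3 | 77% | 5.0% | 4.7% |
| micrograms | 99% | 5.0% | 4.7% |

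The microgram row only illustrates the scaling. Nothing in the article suggests that unit.

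**Step 4: mixed models.** A random-intercept Poisson model with a constant arm effect rejected in about 7% of 150 simulated trials. Its Monte Carlo standard error is √(0.07 × 0.93 / 150) = 0.021, so the rate lies between about 3% and 11%, a range that includes 5%.

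**The case against.** **The endpoint is exploratory.** This is correct, and it limits the consequences. No confirmatory conclusion can rest on the 72 h total, and the primary endpoint uses linear regression. The label concerns multiplicity, however, and does not make a wrong standard error right. The plan still promises an interval and a 0.05 threshold for this result.

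**The size is assumed.** This also stands. The article supplies no consumption data, and mg is an inference. A reader might conclude that a false positive is more likely than not. That does not follow: the assumed range starts at 38%, and the error vanishes for small spread or a coarse unit. Only the unit dependence is free of assumptions.

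**The mixed models are not shown to be broken.** A reader might infer that the repeated-consumption analyses fail in the same way, including the opioid model, which is described ahead of the exploratory endpoints and so may be in the hierarchy (Fig. 3 is not shown). The documents do not support that. The patient random effect takes up most of the between-patient variation, the listed fixed effects contain no arm-by-time term, and the check of a constant arm effect was compatible with 5%. The unstructured covariance, if it acts at visit level, would free the variances further.

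**Opioid sparing as the main mechanism.** A reader might raise the stakes this way, but the article does not say it. It presents pain itself as impairing recovery.

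**A full SAP may specify a robust variance.** It may. As written, though, the article names a distribution unsuited to the outcome, which is a choice made and not a detail left open.

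**Conclusion.** The point holds for the 72 h morphine-equivalent total. Plain Poisson regression makes its p-value and interval depend on an unstated unit, and this is exact algebra. That the interval is too narrow depends on the SD exceeding the square root of the mean. Under the assumed range of mean 20/SD 10 to mean 60/SD 40 in mg, the standard error is 2.2 to 5.2 times too small and type I error is about 38% to 70%.

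For the opioid and non-opioid mixed models it is a lesser point, since the planned constant arm effect appears close to correctly calibrated. The primary QoR-15 analysis is untouched. This should be corrected before analysis, but it does not threaten the trial's main conclusion.

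**What to change.** State the unit and the reference route for morphine equivalents. For the 72 h total, keep the log link, so that the estimate remains a ratio of means, and specify a quasi-Poisson or robust (sandwich) variance. Intervals will be wider where consumption is overdispersed, and the interval for the ratio will no longer depend on the unit.

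For repeated opioid and non-opioid consumption, a log-link GEE with robust standard errors can be used as a precaution. A linear model on log(mg + 1) is not a suitable substitute: the added constant makes both the estimate and its standard error depend on the unit.

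The cost is a sentence or two in the analysis section and a different call in R, with no new data and no change to the sample size.
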